#### Post-treatment clinical assessment

Performed by a blinded rater according to the pre‐treatment clinical assessment visit on the same day of the last treatment (V7):

FMA‐UERelative grip strength measurement (vigorimetry)Stroke‐specific Quality‐of‐Life Scale (SS‐QOL)Modified Rankin Scale ScoreBarthel Index

#### Follow-up visit

The last visit will be scheduled 3 months ± 7 days after the last treatment and will be performed by a blinded rater according to the pre‐treatment clinical assessment visit:

FMA‐UERelative grip strength measurement (vigorimetry)Stroke‐specific Quality‐of‐Life Scale (SS‐QOL)Modified Rankin Scale ScoreBarthel IndexNumber of days as an inpatient during the 3 months after the interventionNumber of days in inpatient rehabilitation

### Criteria for discontinuing or modifying allocated interventions {11b}

In the event that the stimulation is not tolerable for the patient, it will be discussed with the patient whether they would like to retry at a later time (within the specified 14 days after the stroke event, s. eligibility criteria) or whether the study participation will be terminated. Modifications of the intervention are not planned to be performed.

Reasons for premature termination of an individual trial subject are:DeathWithdrawal of consentPatient lost to follow‐upMajor protocol violationOccurrence of an Adverse Event or a Severe Adverse Event (e.g., seizures) that prevent the patient’s further safe participation in the trail.If, in the investigator’s opinion, continuation of the trial would be detrimental to the subject’s well‐being.pregnancyNoncompliance

The PI decides on the withdrawal of a patient from study treatment in case one of the criteria mentioned above occurs. The reason for withdrawal will be recorded in the CRF as well as in the subject’s medical records. Premature termination should be prevented as best as possible. In case a subject withdraws from further participation at their own request, the reasons/circumstances will be determined and documented. All sessions and assessments of the last trial day will be performed and documented as well as the final status of the patient. Each withdrawn patient should enter the follow-up phase. The patient will not suffer any disadvantage in case of requested withdrawal of any further study procedure participation including the follow up.. Adverse Events (AEs)/ Serious Adverse Events (SAEs) should be followed‐up as far as possible.. Patients will be contacted by phone or letter prior to follow‐up examinations. Subjects dropping out after completion of intervention therapy will not be replaced. A final assessment visit for the relevant safety data will be always offered to the patient.

### Stopping rules and exclusion of study centers

Participating centers will be discontinued if their recruitment rate is less than 50% of the agreed recruitment rate indicated in the declaration of commitment at mid-recruitment (15 months into the recruitment period), and either no efforts have been undertaken to improve recruitment rate, or all opportunities for improving recruitment rate have been exhausted. The Data Safety and Monitoring Board (DSMB) has the right to discontinue the trial prematurely, in case of at least one of the following situations: Severe adverse events, substantial changes in risk–benefit considerations, insufficient recruitment.

### Strategies to improve adherence to interventions {11c}

The compliance is expected to be very high as the rTMS treatment is painless and non-invasive, and communicative barriers such as severe aphasia are excluded. Accordingly, in one high-frequency rTMS trial with comparable design only 4/157 (2.5%) subacute stroke patients dropped out because they did not tolerate the treatment [21].

### Relevant concomitant care permitted or prohibited during the trial {11d}

During the study, all patients will receive standard conventional rehabilitation treatment including occupational therapy after TMS treatment for 40 min, 5 times per week. The treatment includes task‐oriented training that involves active participation of the affected limb and individualized motor task training. Subsequently, exercise training, including active‐assistive range of motion exercise of the affected extremity, holding, moving, releasing of cups and cubes, will be administered by the same therapists.

According to the exclusion criteria participation in competing trials or therapeutic interventions other than conventional rehabilitation treatment procedures with effect on motor recovery, will have to result in termination of study participation. Patients are informed about the regulations before giving informed consent.

### Provisions for post-trial care {30}

There will be no special procedures following for patients that have completed the trail. Patients will be treated according to the standard of care after the termination of the study. After the last treatment, the subject enters the Follow‐up phase. For patients prematurely terminating the study for one of the above listed reasons, there will be no special follow‐up procedures. In case of a premature termination of therapy, reasons/circumstances and if applicable the final status will be documented. If the patient does not withdraw the consent for further Follow‐up, he/she should be followed‐up as planned. To those who suffer harm from trial participation (e.g., epileptic seizure, headache), the standard treatment for the symptoms that have been arisen will be provided in the hospital.

### Outcomes {12}

#### Primary clinical endpoint

Primary efficacy endpoint is the motor performance after the intervention, as assessed by the Fugl‐Meyer assessment of the upper extremity (FMA‐UE). The upper‐extremity (UE) portion of the Fugl‐Meyer assessment (FMA‐UE, range 0‐66, 0 = no motor function, 66 = normal motor function) is the most frequently used scale to quantify post‐stroke motor recovery of the upper extremity [23] and correlates well with subjective assessment of motor function. The FMA‐UE was used as an endpoint in most of the recent high‐frequency rTMS trials in early subacute stroke patients [18–21]. For these reasons, the FMA‐UE immediately after the last treatment session was chosen as the primary outcome measure of this trial.

#### Secondary endpoints

Motor performance 3 months after the intervention, as assessed by the FMA‐UE [24].Relative grip strength measured with a vigorimeter. Grip strength is an additional robust measure that can be quantified easily by vigorimetry (measured in kg). Relative grip strength is defined as of the maximum grip strength of the affected hand divided by the maximum grip strength of the unaffected hand. It is unaffected by compensatory movement strategies, and has been successfully used in stroke trials previously [25].Stroke‐Specific Quality‐of‐Life Scale (SS‐QOL). The SS‐QOL is a patient‐centered outcome measure designed to provide an assessment of health‐related quality‐of life specific to patients with stroke [26, 27].Modified Rankin Scale (mRS) score. The modified Rankin Scale (range 0‐6, 0 = no disability, 6 = death) is the most widely used scale for measuring the degree of disability or dependence in the daily activities of people who have suffered a stroke [28].Barthel Index (BI). The Barthel index (ordinal scale 0‐100, 0 = fully dependent, 100 = independent in feeding, walking and grooming) [29] is an index of independence in activities of daily living and is used to monitor functional outcome during neurorehabilitation in stroke [30].Number of days as an inpatient during the 3 months after the intervention.Number of days in inpatient rehabilitation.

All the above endpoints have been previously validated and are listed in the relevant stroke treatment guidelines [24–30]. Assessments will be performed before, immediately after, and 3 months after the intervention to capture short‐ and long‐term effects by a rater blinded to treatment condition. Additionally, the number of days as an inpatient during the 3 months after the intervention is considered as a socioeconomically relevant measure of how quickly a patient can return to his/her home environment.

### Participant timeline {13}

The study is planned to span a total duration of 42 months, between November 2022 and May 2026. The TMS intervention duration for each subject is 1 week (5 sessions per week). The maximum study duration including screening, MRI scan, TMS intervention and a 3-month follow-up measurement for each subject will be 3.5 months. The time course of events can be seen in Table 1.

**Table 1 Tab1:** Flow chart of visits and events

**Events**	**Screening (V1)**-14 days to -1 day prior 1th treatment	**Treatment (V2-6)** (treatment will be performed on 5 following working days)	**Post –treatment (V7)**^**g**^ (last treatment and post- treatment visit will be performed on the same day)	**Follow-up (V8)**^**g**^(after 3 months ± 7 days)
Study Entry				
Informed Consent (IC)	X	–	–	–
Inclusion/Exclusion Criteria	X	–	–	–
Physical and neurological examination	X	–	–	–
Medical History	X	–	–	–
Pre-treatment clinical assessment^a^	X^f^	–	–	–
TMS and EEG measurement^b^	X^f^	–	–	–
MRI^c^	X	–	–	–
Randomization^d^	X	–	–	–
TMS and physiotherapy sessions	–	X	–	–
Post-treatment assessment^a^	–	–	X	–
Post-treatment follow-up assessment ^e^	–	–	–	X
Adverse Events	–	Start of study treatment or after first treatment and until 7 days after discontinuation from treatment		

^a^pre & post treatment assessment and tests: Fugl‐Meyer Assessment upper extremity (FMA-UE); grip strength; SS‐QOL; Rankin Scale; Barthel Index. For screening, FMA-UE and grip strength should be repeated within 3 days prior first treatment (V2), if the screening was done earlier

^b^Each center will send the EEG raw (32‐channel) data to the coordinating center. It is sufficient that appropriate data from a standard EEG measurement is available. This can also be from an examination before screening

^c^MRI is not mandatory for inclusion, but a sufficient imaging should be available before start of treatment (please

see section “screening visit V1” for more details)

^d^in case of eligibility the randomization will take place at the end of the screening

^e^post treatment follow-up assessment and tests: FMA-UE; grip strength; SS‐QOL; modified Rankin Scale; Barthel Index; number of days as an inpatient during the 3 months after the intervention

^f^ TMS, EEG (32‐channel) and Pre‐treatment clinical assessment at screening should be repeated within 3 days prior first treatment (V2), if done earlier. Standard EEG is not relevant for inclusion and can be performed at any time, also before screening

^g^Performed by a blinded rater

### Sample size {14}

It is planned to recruit 144 patients for the study. This corresponds to a recruitment rate of approximately 10 patients per study site and year. The primary objective is to establish whether personalized stimulation (Experimental Condition) is superior to non-personalized stimulation (Control Condition 1) and sham stimulation (Control Condition 2) regarding differences in FMA-UE at the end of intervention. A mean FMA-UE at baseline of 33 ± 12 [31] is expected. From the guideline [24] a minimal clinically significant improvement of 12 points on FMA-UE is derived, which leads to an effect size of 1.0. However, an effect size of 0.67 instead of 1.0 will be conservatively assumed, as a large placebo effect in the sham condition might be observed, and also in the non-personalized stimulation condition. The analysis will be done as an analysis of covariance (baseline adjusted) with overall F-test for the factor “study arm”. If the F-test is significant, according to the closed testing procedure (Hochberg Tamhane, Multiple Comparison Procedures, New York, 1987) no adjustment for multiple testing will be necessary for pairwise comparisons in the three arm situation. Assuming normal distribution of the primary outcome measure and an R-squared of 0.2 for the covariate (baseline FMA-UE) 36 evaluable patients per arm will be needed and, thus, 108 evaluable patients in total for the F-test (type 1 error 0.05, power 80%). This is based on the worst case scenario of an effect size for non-personalized stimulation = 0.67/2 = 0.335. Thus, on the one hand, it is ensured that in the case of unexpectedly positive results of the non-personalized stimulation, there will be enough power to proceed to subsequent pairwise comparisons. On the other hand, if standardized differences between study arms of 0.67 hold, there will be a power of 88% to confirm these differences (type 1 error 0.05, two-sided). To adjust for degrees of freedom for center, baseline, and 20% dropouts, 144 patients will be included, i.e., 48 per study arm. The sample size calculation was performed by PASS 2020.

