### Explanation for the choice of comparators {6b}

The comparison between the Experimental Condition and Control Condition 1 will reveal to what extent brain‐oscillation‐synchronized rTMS is more effective than non‐brain oscillation‐synchronized but otherwise identical rTMS, i.e., it will address the comparison of primary interest in this trial. The comparison between the Experimental Condition and Control Condition 2 will address the important question to what extent it is the real brain stimulation rather than somatosensory and auditory inputs synchronized to the ongoing brain oscillation that causes the therapeutic effect. Use of a combined active/passive stimulation coil with realistic auditory and somatosensory stimulation enables stimulation that blinds both the patient and the treatment provider to the condition.

The dose (number of stimuli per session, number of sessions) was adopted from previous stroke trials that used high‐frequency rTMS of the ipsilesional motor cortex in early subacute stroke patients [18–21].

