In case of the confirmation of the main hypothesis for the primary endpoint of this trial, i.e., brain-oscillation-synchronized rTMS results in a higher FMA-UE immediately after the last treatment session compared to the two control conditions, non-brain-oscillation-synchronized rTMS and sham rTMS, a confirmatory trial will be conducted. The confirmatory trial will seek to provide firm evidence for efficacy and safety of brain-oscillation synchronized rTMS in an even broader range of early subacute stroke patients with a broader variety of arm-/hand dysfunction severity. The anticipated clinical impact of the confirmatory trial is to provide firm evidence for superiority of brain-oscillation-synchronized personalized therapeutic brain stimulation with respect to clinically relevant outcome of arm-/hand function in early subacute stroke patients. If successful this will lead to a significant expansion of the treatment repertoire of this patient population in the early neurorehabilitation setting.

In summary, the results of this trial will be of outstanding importance for the establishment of novel personalized brain‐oscillation synchronized rTMS therapy protocols, which likely will lead to a paradigm shift in non-invasive brain stimulation. This new therapy option will lead to a significant expansion of the recovery repertoire of patients suffering from a stroke in the early neurorehabilitation setting that might be expanded to a variety of other deficits (e.g., aphasia or neglect) and other brain network disorders in further confirmatory trials.

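### The stated 88% is the power of one ungated pairwise test, not of the objective to beat both controls; in the scenario that sets N, that objective has about 34% power

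*Protocol article*

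**What the plan says.** All of the power figures are in the protocol article, Sample size {14}.

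- **Objective.** "The primary objective is to establish whether personalized stimulation (Experimental Condition) is superior to non-personalized stimulation (Control Condition 1) and sham stimulation (Control Condition 2"), judged on FMA-UE at the end of the intervention. Superiority over both controls is therefore required.
- **Main contrast.** In Explanation for the choice of comparators {6b}, personalized versus non-personalized is singled out: "it will address the comparison of primary interest in this trial".
- **Assumed effect.** "an effect size of 0.67 instead of 1.0 will be conservatively assumed".
- **What sets N.** 36 evaluable patients per arm (108 in total) give 80% power for the F-test, with R-squared 0.2 for baseline. "This is based on the worst case scenario of an effect size for non-personalized stimulation = 0.67/2 = 0.335". The section adds that this secures enough power to reach the pairwise step if non-personalized stimulation does unexpectedly well.
- **Pairwise power.** "if standardized differences between study arms of 0.67 hold, there will be a power of 88% to confirm these differences".
- **Procedure.** Methods and analyses {20a, 20b, 20c, 21b} tests the three-arm F-test first. Unadjusted pairwise comparisons follow if it is significant; otherwise their p-values are descriptive only.
- **Consequence.** According to the Discussion, if personalized stimulation does better than the two control conditions on the primary endpoint, "a confirmatory trial will be conducted".

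**The concern.** The 80% and the 88% are the only powers given, and they sit directly beside an objective that needs two pairwise wins after a significant F-test. The plural in the 88% sentence invites the reader to take that figure as the chance of confirming both differences.

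The scenario that fixes N also places non-personalized stimulation halfway between sham and personalized. The contrast of primary interest is then 0.335, not 0.67, and no power is given for it.

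At stake is how the result is read. A significant F-test with a non-significant main contrast could be taken to mean that synchronization adds nothing, and under the Discussion it would not trigger the confirmatory trial. Readers need to know how likely that outcome is when synchronization does have an effect.

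**Working it through.** **Inputs** (Sample size {14}; allocation from Intervention description {11a}; gate from Methods and analyses): 36 evaluable per arm, 1:1:1; two-sided type 1 error 0.05; R-squared 0.2, so residual variance is 1 − 0.2 = 0.8 in units of the unadjusted SD; error df 108 − 3 − 1 = 104.

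**1. Reproduce the 80%.** Effects 0 / 0.335 / 0.67 have mean 0.335. Noncentrality = 36 × (0.335² + 0² + 0.335²) / 0.8 = 36 × 0.22445 / 0.8 = 10.10. Noncentral F with 2 and 104 df gives 80.8%; 35 per arm gives 79.5%, so 36 is the minimum. With R-squared 0 the power would be 70.9%, which supports this reading of the inputs.

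**2. Reproduce the 88%.** For one contrast at 0.67, the standard error is √(0.8 × 2/36) = 0.2108, so the noncentrality is 0.67 / 0.2108 = 3.178. Power is 88.3% on 104 df, 88.0% on the two-arm 69 df and 88.8% by the normal approximation. This is one contrast with no F-test gate.

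**3. Power of the procedure as planned.** A simulation of 400,000 trials per scenario counted trials in which the F-test was significant and the pairwise test or tests were significant in favour of personalized stimulation. The ungated column is from the noncentral t; for 0.335 the noncentrality is 0.335 / 0.2108 = 1.589.

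| True effects: sham / non-personalized / personalized | F-test | Personalized vs non-personalized, ungated | Same, gated | Personalized vs sham, gated | Both controls, gated |
|---|---|---|---|---|---|
| 0 / 0 / 0.67 | 91.0% | 88.3% | 85.7% | 85.6% | 80.3% |
| 0 / 0.335 / 0.67 (sets N) | 80.8% | 35.0% | 34.1% | 80.1% | 33.8% |

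In the second row, the F-test power (80.8%) is almost the same as the gated power of the sham contrast (80.1%), so the sham contrast carries it.

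**4. When would 88% be the joint power?** Effects 0 / 0.67 / 1.34 give 88.3% for both controls. That needs personalized stimulation to exceed sham by 1.34, which is twice the assumed 0.67 and above the 1.0 that the section marked down.

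**5. Sensitivity of the 34%.** With 38 per arm (48 × 0.8 = 38.4), the gated main contrast has 35.8% and both controls 35.5%. With all 48 per arm, the figures are 44.1% and 43.9%. Charging six covariate df instead of one leaves the 36-per-arm figure at 34.2%. Reaching 80% at a difference of 0.335 needs about 113 evaluable per arm (112 gives 79.8%, 114 gives 80.5%).

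**6. Outcomes in the scenario that sets N.** A significant F-test without a significant main contrast occurs in 80.8 − 34.1 = 46.7% of trials, or 46.7 / 80.8 = 58% of those with a significant F-test.

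**The case against.** The strongest reply is that nothing is miscalculated and both figures carry their conditions: the 80% is labelled as F-test power, and the 88% depends on differences of 0.67. That stands, and a reader who inferred an arithmetic error would be wrong.

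Three further inferences are tempting and are not supported.

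- **That the assurance about reaching the pairwise step is false.** It promises only passage through the F-test, and 81% bears it out.
- **That the trial is underpowered for its objective in every scenario.** The assumed 0.67 can be read as the advantage over each control, because the section allows for a placebo effect in both. With non-personalized equal to sham, power for both controls is about 80%.
- **That the trial will mostly pass the F-test and then fail on its main question.** In the 0.335 scenario this is the commonest single outcome, but at 47% it is under half.

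It is also fair that the trial is labelled exploratory, that 95% confidence limits for between-arm differences are already planned, and that a condensed article may leave further power figures to the full protocol. Silence about the 0.335 contrast would not be a finding on its own account. But the 88% sentence is in the article and attaches to confirming the differences, which the planned procedure does not deliver at that level. The exploratory label changes neither the stated objective nor the Discussion's trigger. The worst-case label also fits only the F-test: for a fixed spread of 0.67, the midpoint minimizes F-test power, while power for the main contrast keeps falling as non-personalized stimulation moves above 0.335.

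**Conclusion.** The power statement is wrong as written: it is not the power for the stated objective. The F-test figure and the single-contrast figure are themselves correct. Under the gated procedure with 36 evaluable per arm:

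- if non-personalized equals sham, power is about 86% per comparison and about 80% for both controls, against the stated 88%;
- in the scenario that sets N, power is about 34% for personalized versus non-personalized and about 34% for both controls, rising to about 44% if all 48 per arm are evaluable.

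These results rest on normality, equal variances, R-squared 0.2 and the protocol's own standardized effects. They describe the two scenarios in the section and do not say which is true. The 0.335 scenario is not remote on the protocol's own terms, since it fixes the sample size and Background and rationale {6a} cites a probable benefit of conventional rTMS.

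**What to change.** In Sample size {14}, with N kept at 144:

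1. Replace the 88% statement with: if non-personalized stimulation equals sham and personalized stimulation exceeds both by 0.67, power after the F-test is 86% per comparison and 80% for superiority over both controls.
2. Add: in the scenario with effects 0, 0.335 and 0.67, the sample size secures only the F-test step (81%); power is about 34% for personalized versus non-personalized and about 34% for superiority over both controls.
3. Keep the assurance about proceeding to pairwise comparisons, but limit it expressly to the F-test.
4. State that a non-significant personalized versus non-personalized contrast after a significant F-test is not evidence that synchronization adds nothing. It can be read with the 95% confidence interval already planned.

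The cost is a few sentences. Sample size, analysis and conduct are unchanged; the stated power becomes less favourable.
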